### 3.2 Primary and secondary endpoints

The primary endpoint measuring postoperative morbidity will be assessed using the CCI within 90 postoperative days.

Secondary endpoints are the following:

- Most severe postoperative complications will be measured using the Clavien classification within 90 postoperative days.
- Specific complications of PD will be recorded:
  - SSI, further divided into 'superficial', 'deep' and 'organ-space' according to the specific anatomic involvement and the Centers for Disease Prevention definition.
  - POPF are classified into three grades, A, B and C, according to the consensus of the International Study Group for Pancreatic Surgery (ISGPS).
  - DGE, which is classified into three grades, A, B and C, according to the consensus of the ISGPS.
  - PPH, which is also classified into three grades, A, B and C, according to the consensus of the ISGPS.
  - Biliary fistula (no standard definition)
  - Gastrojejunal anastomosis fistula (no standard definition)
  - Pancreatitis (no standard definition)
- Length of stay will be measured from operative day until discharge.
- Readmissions will be counted until postoperative day 90.
- Patients' QoL will be assessed by the EORTC (European Organisation for Research and Treatment of Cancer) QLQ-C30 questionnaire. This questionnaire will be filled 4 times: at preoperative consultation or admission, at patient's discharge, between the 4th and 6th postoperative week and on POD 90 (via phone call).
- The subjective tolerance of EEN will be assessed daily during the first 7 postoperative days, using a visual analogue scale (0-10). Objective tolerance will be assessed by the amount of EEN as a percentage (tolerated/total amount of EEN required).
- Time required (in days) to reach respectively 50% and 100% of the daily caloric targets required (30 kcal/kg/day if BMI <30 kg/m^2 and 25 kcal/kg/day if BMI ≥30 kg/m^2, protein target: 1.5 g/kg/day).
- Metabolic response to EEN will be assessed with biological measurements preoperatively and twice weekly (currently already measured, according to our PD care map):
  - C-Reactive Protein (CRP) and procalcitonin
  - Simple blood count, coagulation
  - Electrolytes: sodium, potassium, calcium, magnesium, phosphate
  - Creatinine, urea, blood glucose, liver and pancreatic function tests, prealbumin,

[figure not shown]

albumin, triglycerides

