#### **4.3 Study procedures**

Given the rate of annual procedures, a recruitment of about 60% of eligible patients, and based NUTRIWHI Trial  
Version 5.0, 20/10/2023

[figure not shown]

on the experience of two randomized studies successfully completed in the Visceral Surgery Department (NCT0508300, NCT00512213), the planned overall study duration is three years including the recruitment period and follow-up. For patients the study duration will be from enrolment until POD 90, date of last follow-up phone call. The expected hospitalization duration for each patient will be approximately 14 days, which is the current mean hospital stay after PD in our department.

Eligibility of the patients will be confirmed on the day before the operation (day -1). Then, patients will be randomized before the operation (day -1) in either the control arm or the experimental one (EEN).

Standardized surgical procedure in all eligible patients: In terms of surgical details, all patients will receive a prophylactic dose of antibiotics (cefuroxime) 30 minutes before incision and first have exploratory laparotomy followed by conventional or pylorus-preserving PD. Pancreaticojejunostomy will be performed. End-to-side hepaticojejunostomy will be performed with single-layer interrupted sutures. A gastrojejunostomy will finally be constructed. Two perianastomotic drains will be placed.

Specific study procedure: At the end of surgery (after the three anastomoses are finished but before closure of the abdomen) and in the EEN study group only, a polyurethane single or double lumen feeding nasojejunal tube (Freka®) 8F will be inserted by the anesthesiologist and placed under direct palpation and visual control by the surgeon, 30 cm distally to the gastrojejunostomy into the jejunum. The tube will be attached according to current practice to the nose wing with a tape. The patient will therefore be under general anesthesia during tube insertion and no x-ray control will be needed.

Postoperatively, patients will receive standardized perioperative care according to the ERAS protocol in both arms.

From a nutritional point of view, this includes:

- The day before surgery: 2 carbohydrate drinks of 200 ml
- The operative day: 2 carbohydrate drinks of 200 ml up to 2 hours preoperatively, then postoperative free drinks
- On postoperative day (POD) 1: bouillons, creams, yogurts, drinks  $\geq 2l$
- On POD 2: light diet, drinks  $\geq 2l$
- On POD 3: normal diet (half portion)

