## **5 STATISTICS AND METHODOLOGY**

### **5.1. Statistical analysis plan and sample size calculation**

A statistician was involved in the study design and estimate of the sample size.

Null hypothesis  $H_0$ : EEN has no effect on postoperative complications (CCI) in the population (and therefore the observed effect is entirely due to chance):  $p_2 = p_1$

Scientific hypothesis  $H_1$ : EEN has an effect on postoperative morbidity (CCI) in the population (and therefore the observed effect is not entirely due to chance):  $p_2 > p_1$

According to a previous randomized trial including a series of PD and assessing a realimentation process (enteral vs. parenteral), the mean CCI was impacted of about 30% (32.8 vs. 24.2). Another study reported a mean CCI of 38 after PD.

Based on the above results, we hypothesize that EEN will reduce by 30% a mean CCI of 35 (+/- 20) of the oral nutrition group. We will therefore expect a mean CCI for the treatment group (EEN) of 24.5 (SD 20). In this superiority study, for a power of 80% and a significance level of p-value  $\leq 0.05$  (two-sided alpha), we will therefore need 57 patients per group according to the sample size calculation. Nevertheless, we will increase the sample size to a total of 144 patients to take into account 20% of drop-outs (e.g., due to non realization of pancreatoduodenectomy or consent withdraw) at 90 days (primary endpoint evaluation). We will therefore need to enroll 72 patients per group in the trial.

The study will be closed once the required 144 patients will be included. No interim analysis will be performed.

Normality of distribution will be determined by the Kolmogorov-Smirnov test and quantile-quantile plots of dependent variables for all continuous variables.

We will use a Student *t*-test to evaluate if the primary outcome (CCI) can significantly be reduced by EEN compared to the control group (comparison of mean CCI hypothesizing a normal distribution). For the analysis of all secondary endpoints, we will also use *t*-tests or chi-squared tests based on the variable types. Regarding the questionnaires filled 4 times during the study, tests specific to repetitive ordinal measures will be used.

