| EORTC QLQ-C30                            | x**          | x**   |              |          |                 | x               | x         | x  |
| Subjective tolerance (VAS 0-10)          |              |       |              | x        |                 |                 |           |    |
| Complications - CCI                      |              |       |              |          |                 | x               | x         | x  |
| Complications - Clavien                  |              |       |              |          |                 | x               | x         | x  |
| LOS                                      |              |       |              |          |                 | x               |           |    |
| Readmissions                             |              |       |              |          |                 |                 |           | x  |

Demographics include the measure of serum CA 19-9 at admission in case of pancreatic cancer.

**EEN:** early enteral nutrition, **EORTC:** European Organisation for Research and Treatment of Cancer, **VAS:** Visual Analog Scale, **CCI:** Comprehensive Complication Index, **LOS:** length of stay, **POD:** postoperative day.

‡ **Metabolic tests:** CRP, procalcitonin, simple blood count, coagulation tests, electrolytes (sodium, potassium, calcium, magnesium, phosphate), creatinine, urea, blood glucose, liver and pancreatic function tests, prealbumin, albumin, triglycerides.

Ω **Nutrition tests:** folate, magnesium, iron, ferritin, transferrin saturation, vitamin D, calcium, phosphate and parathormone, vitamin E, HbA1c (glycated hemoglobin).

° **Body measures:** lean body mass using bioelectrical impedance analysis and strength using handgrip.

\* Filled either during screening visit or at hospital admission.

\*\* The preoperative EORTC questionnaire will be filled during screening visit or on hospital entry day. In total, four questionnaires will be filled. The last one on postoperative day 90 will be filled by the study nurse who will perform the phone call.

\*\*\* At the end of surgery and in the EEN study group only: polyurethane single or double lumen feeding nasogastric tube (Freka®) 8F.

^ Discharge on day 14: current mean hospital stay.

[figure not shown]

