**Service de chirurgie viscérale**

[name], Chef de Service

[name]

[name]

A maximum of six months is permitted between the screening and the intervention. If the interval is longer, a new (more recent) consent form will be signed.

The calorimetry should ideally be performed between POD 3 and POD 7. The accepted period to perform the calorimetry taking into account the clinical variability is between POD 3 and POD 30.

The visit n°4 should ideally be performed between POD 30 and POD 45. The accepted period to do the visit n°4 taking into account the clinical variability is between POD 20 and POD 60.

The visit n°5 should ideally be performed on POD 90. The accepted period to do the visit n°5 taking into account the clinical variability is between POD 75 and POD 115.

The most important questionnaire is the questionnaire of the visit n°5 on POD 90. If this questionnaire is not performed, it will be considered a deviation to the protocol. Absence of other questionnaires will not be considered as protocol deviation.

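### The quality-of-life analysis puts the preoperative QLQ-C30 form in with the repeated measures and states no between-arm contrast; using it as a covariate would be a free gain in power

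*Protocol*

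**What the plan says.** Section 5.1 first gives a general rule: "For the analysis of all secondary endpoints, we will also use *t*-tests or chi-squared tests based on the variable types". It then makes an exception for quality of life: "Regarding the questionnaires filled 4 times during the study, tests specific to repetitive ordinal measures will be used". This is the only text on how quality of life is analysed. It names a class of test, but no specific test, no arm comparison and no role for the first form.

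Section 3.2 gives the timing: "This questionnaire will be filled 4 times: at preoperative consultation or admission", then at discharge, in postoperative weeks 4 to 6, and by telephone on postoperative day (POD) 90. A footnote to the Appendix 1 schedule confirms that the preoperative form is counted: "In total, four questionnaires will be filled".

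Section 4.3 places randomisation on the day before surgery. Section 3.4 starts enteral feeding six hours after the operation. Under section 5.1, only the responsible surgeon knows the allocation before surgery.

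The notes after the Appendix 1 schedule add: "The most important questionnaire is the questionnaire of the visit n°5 on POD 90". They make a missing POD 90 form a protocol deviation, and exempt the other forms from that rule.

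**The concern.** The objective in section 3.1 is the impact of early enteral nutrition on quality of life, which is a question about the difference between arms. Read literally, a test for repeated ordinal measures may test only change over time within patients. Friedman's test is one example, and it has no arm factor. An analyst could follow the sentence and leave the objective unanswered.

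If an arm factor is added, the preoperative form still sits inside the series. Neither feeding nor knowledge of the allocation can have influenced it, so its expected arm difference is zero. As an outcome it pulls an overall arm effect towards zero. As a covariate it would remove between-patient variation and sharpen the comparison. The same data can therefore weaken or strengthen the analysis, and the protocol does not say which use is meant. What is at stake is missing a real difference in a secondary endpoint.

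**Working it through.** **Plan's own figure.** The protocol gives no power figure for quality of life. The 57 per arm used below is its evaluable number for the primary endpoint. It reproduces as 2 × (1.96 + 0.8416)² × 20² / 10.5² = 56.95, rounded up to 57; 57 / 0.8 = 71.25, rounded up to 72 per arm, or 144 in total.

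**Assumptions (not in the protocol).** A score with SD 1 at every form, the same correlation ρ between any two forms (0.5, range 0.3 to 0.7), a postoperative arm effect d = 0.4 SD, and n = 57 complete sets of forms per arm. The test is two-sided at 5%, with power from the non-central chi-square. Critical values are 3.841 (1 df) and 7.815 (3 df); λ is the non-centrality. The arm differences δ run in the order preoperative, discharge, weeks 4 to 6, POD 90.

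**Dilution.** With δ = (0, d, d, d), the four-form average is 3d/4, or 75% of d. With the effect at one form only it is d/4, or 25%.

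**Constant effect, ρ = 0.5**

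1. Arm effect over four forms. Effect 0.75 × 0.4 = 0.30; variance (1 + 3ρ)/4 = 0.625. λ = 57 × 0.30² / (2 × 0.625) = 4.10, 1 df: power 53%.
2. Arm-by-time test. λ = n / (2(1 − ρ)) × Σ(δ − mean δ)² = 57 × 0.12 = 6.84, 3 df: 58%.
3. Mean of the three postoperative forms, unadjusted. Variance (1 + 2ρ)/3 = 0.667. λ = 57 × 0.16 / (2 × 0.667) = 6.84, 1 df: 74%.
4. The same mean, adjusted for the preoperative score. Variance (1 + 2ρ)/3 − ρ² = 0.417. λ = 57 × 0.16 / (2 × 0.417) = 10.94, 1 df: 91%.
5. Adjusted joint test of the three postoperative differences. λ = n / (2(1 − ρ)) × [Σδ² − ρ(Σδ)² / (1 + 3ρ)] = 57 × (0.48 − 0.288) = 10.94, 3 df: 80%.

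Taking the preoperative form out of the outcome moves power from 53% to 74%. Using it as covariate moves it on to 91%.

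**Range of correlation, constant effect**

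| Analysis | ρ = 0.3 | ρ = 0.5 | ρ = 0.7 |
|---|---|---|---|
| Four-form arm effect | 64% | 53% | 44% |
| Arm-by-time, 3 df | 43% | 58% | 82% |
| Adjusted postoperative mean | 89% | 91% | 97% |
| Adjusted joint test, 3 df | 77% | 80% | 91% |

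**Other effect patterns, ρ = 0.5, same formulas**

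| Analysis | POD 90 only | Discharge and weeks 4 to 6, gone by POD 90 |
|---|---|---|
| Four-form arm effect | 10% | 27% |
| Adjusted postoperative mean | 20% | 60% |
| Arm-by-time, 3 df | 58% | 72% |
| Adjusted joint test, 3 df | 61% | 80% |
| Adjusted POD 90 difference alone | 69% | 5% |

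The POD 90 line uses variance 1 − ρ² = 0.75. With an effect at POD 90, λ = 57 × 0.16 / (2 × 0.75) = 6.08, so power is 69% under the constant pattern too. In every pattern, each adjusted analysis beats its unadjusted counterpart (mean against mean, 3 df against 3 df). Between adjusted analyses, the best one depends on the pattern.

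**The case against.** The strongest reply is that the sentence is vague rather than wrong. It does not say that the preoperative form is an outcome, that the four forms are averaged, or that an omnibus test is run. A repeated-measures method can take the first form as baseline and can yield a difference at any visit. The exact model and contrast often belong in a statistical analysis plan, which may exist and is not shown here. This stands as far as it goes, and it is why the dilution is conditional. It does not remove the point: section 5.1 does fix a class of method for the whole series of four forms, and nothing in it leads the analyst to an arm comparison or to a baseline role for the first form.

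Three stronger readings are tempting, and the documents do not carry them.

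- A reader might infer that the protocol declares the POD 90 arm difference its main quality-of-life result and then fails to test it. The Appendix 1 note ranks a questionnaire within a rule on protocol deviations. It ranks no arm difference, and section 3.2 lists the four forms without priority.
- A reader might infer that POD 90 should be the only test. That is a choice of estimand. Feeding stops once oral intake passes half of requirements (section 3.4), so a fading effect is plausible. In that case a POD 90 test has only the 5% of a null result.
- A reader might object that no QLQ-C30 score is named and that many could be tested. Choosing the score is ordinary content for a statistical analysis plan, and the protocol does not give the number of scores.

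**Conclusion.** The point holds in a limited form. Section 5.1 assigns all four forms, including one that feeding cannot affect, to an unnamed class of repeated-measures test and states no between-arm contrast. If the preoperative form is handled as an outcome, the loss is material: 53% or 58% power against 91% or 80% in the base illustration. For the four-form average against the adjusted postoperative mean, the comparison runs from 64% against 89% at correlation 0.3 to 44% against 97% at 0.7.

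These figures rest on assumed values for the effect, the correlation and the number of complete sets of forms, and on a normal approximation. The 91% belongs to the adjusted postoperative mean and must not be read as the power of a POD 90 test. The gain from adjustment is small for some patterns: 61% against 58% for the 3 df tests when only one form is affected.

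This is a free improvement to a secondary endpoint. The sample size of 144 and the primary comparison of the Comprehensive Complication Index do not change.

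**What to change.** Replace the quality-of-life sentence in section 5.1 with text to this effect: quality of life is compared between arms in a repeated-measures model; the outcomes are the discharge, week 4 to 6 and POD 90 forms; the preoperative score is a covariate; arm, time and arm-by-time are effects; the arm difference is reported with its 95% CI at each visit, including POD 90. If the sponsor regards the chosen score as ordinal, an ordinal repeated-measures regression can have the same structure.

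The sponsor should prespecify which score is used and whether the POD 90 difference or the postoperative mean is the headline contrast. The tables show what each choice gains and gives up.

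The cost is one paragraph, with no new data or visits. The preoperative form becomes an adjustment variable, and its absence is not currently a deviation. Section 5.2 already foresees considering multiple imputation for adjustment variables with more than 5% missing, so a cross-reference there is enough.

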## 5.2. Handling of missing data and drop-outs

In case of missing data among variables other than endpoints (adjustment variables, >5% of expected data) we will consider the use of the multiple imputation technique. This process will be performed multiple times (e.g., 10-20 times) to combine multiple data sets to produce one final data sets replacing the missing data.

A 20% drop-out was considered in the sample size calculation.

## 6 REGULATORY ASPECTS AND SAFETY

### 6.1 Local regulations / Declaration of Helsinki

This study is conducted in compliance with the protocol, the current version of the Declaration of Helsinki, the ICH-GCP, the HRA as well as other locally relevant legal and regulatory requirements.

### 6.2 Serious Adverse Events and notification of safety and protective measures

An Adverse Event (AE) is any untoward medical occurrence in a patient or a clinical investigation subject which does not necessarily have a causal relationship with the trial procedure. An AE can therefore be any unfavourable or unintended finding, symptom, or disease temporally associated with a trial procedure, whether or not related to it.

A Serious Adverse Event (SAE) (ClinO, Art. 63) is any untoward medical occurrence that

- Results in death or is life-threatening,
- Requires in-patient hospitalization or prolongation of existing hospitalization,
- Results in persistent or significant disability or incapacity, or
- Causes a congenital anomaly or birth defect

Both Investigator and Sponsor make a causality assessment of the event to the trial intervention, (see table below based on the terms given in ICH E2A guidelines). Any event assessed as possibly, probably or definitely related is classified as related to the trial intervention.

| Relationship                                                                            | Description                                                                                                               |
|-----------------------------------------------------------------------------------------|---------------------------------------------------------------------------------------------------------------------------|
| Definitely                                                                              | Temporal relationship
Improvement after dechallenge*
Recurrence after rechallenge
(or other proof of drug cause) |
| Probably                                                                                | Temporal relationship
Improvement after dechallenge
No other cause evident                                          |
| Possibly                                                                                | Temporal relationship
Other cause possible                                                                             |
| Unlikely                                                                                | Any assessable reaction that does not fulfil the above conditions                                                         |
| Not related                                                                             | Causal relationship can be ruled out                                                                                      |
| *Improvement after dechallenge only taken into consideration, if applicable to reaction |                                                                                                                           |

Investigators make a severity assessment of the event as mild, moderate or severe. Mild means the complication is tolerable, moderate means it interferes with daily activities and severe means it renders daily activities impossible.

### **Reporting of SAEs (see ClinO, Art. 63)**

All SAEs are documented and reported immediately (within a maximum of 24 hours) to the Sponsor of the study.

If it cannot be excluded that the SAE occurring in Switzerland is attributable to the intervention under investigation (related to enteral nutrition), the Investigator reports it to the Ethics Committee via BASEC within 15 days.

If the SAE occurs at one of the study sites, the coordinating Investigator reports the events to the Ethics Committee concerned, within 15 days.

Exemptions from expedited reporting may be possible if the SAE is a clear complication of the operation (pancreatoduodenectomy) not related to the study intervention (enteral nutrition) or if the SAE corresponds to a rehospitalization or prolongation of the hospitalization due to a postoperative complication unlinked to the study intervention (enteral nutrition).

